### Analysis of heterogeneity of treatment (HTE)

HTE was analyzed by both stratified analyses and regression models with interaction terms. HTE of stone clearance was evaluated by stone size (<7mm, 7-10mm, 11-15mm, >15mm) and location (lower pole, non-lower pole, ureter). HTE of PROs was evaluated by patient age group (8-11, 12-15, 16-18, 19-21) and sex. Categories were defined *a priori* by the DOC.

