### Missing data

We used multiple imputation (MI) to handle missing data. Variables used to impute missing data included all baseline covariates, treatment variable, and observed outcomes that were used in the analysis. Twenty imputed datasets were created and analyzed separately, and the results were combined using Rubin's rules to produce valid statistical inferences. MI was used for the analyses of stone clearance, PROs at week 1, and HTE of both primary and secondary analyses.

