### Sensitivity analysis

We conducted a complete data analysis assuming the missingness was completely random. In addition, to assess the impact of potential missing not at random mechanisms on the study results for stone clearance, we performed a sensitivity analysis using pattern-mixture models. We assumed that patients with missing outcomes had different stone clearance rates compared to those without missing data. The scenarios included:

1. Patients with missing outcomes had a 100% stone clearance rate, regardless of the surgery received.
2. Patients with missing outcomes had a 0% stone clearance rate, regardless of the surgery received.
3. Patients with missing outcomes had stone clearance rates ranging from a -25% to 25% change from observed rates within each treatment group.
4. Patients with missing outcomes had stone clearance rates changing oppositely between the two treatments, ranging from 0% to 100%.

We also conducted a sensitivity analysis for the assessment window of the stone clearance outcome using ultrasounds obtained between 0 to 16 weeks, selecting those closest to the 6-week post-surgery time-point. Additionally, we performed a central review of 10% randomly selected post-op images. We calculated the sensitivity and specificity of the misclassification of the primary outcome and updated the weights after incorporating them with IPW to correct bias due to misclassification.

**eFigure 1.** The Pediatric KIDney Stone (PKIDS) Care Improvement Network

[figure not shown]

**eFigure 2.** Ultrasonographic Protocol Agreed Upon by PKIDS Investigators and Implemented as Standard Imaging Follow-Up After Surgical Intervention

EXAMINATION: [ ]

DATE: [ ]

COMPARISON: [ ]

TECHNIQUE: Grayscale sonographic image acquisition was performed of the kidneys and bladder.

FINDINGS:

BLADDER:

Stone visualized at UVJ: [No/Yes]

RIGHT KIDNEY:

Collecting system: [The calyces and pelvis are nondilated.]

Ureter: [The ureter is nondilated.]

Calculi: [No/Yes]

- If calculus present, measure the longest dimension of 3 largest stones

1. Location: [If present, PLEASE DESCRIBE for each measured stone: e.g., upper pole calyx; interpolar calyx; lower pole calyx; renal pelvis; ureteropelvic junction; proximal ureter; distal ureter]

- Size: [ ] mm

- Shadow: [No/Yes]

- Doppler: [Not applicable/Twinkle/No twinkle]

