| Non-lower pole kidney                                                                                                                                                                                                             | 77.3
(54.9- 99.6)        | 57.8
(51.1-64.6) | 19.4
(-3.9-42.8)   |
| Ureter                                                                                                                                                                                                                            | 83.4
(54.1- 100.0)       | 81.1
(77-100.0)  | 2.2
(-27.3-31.8)   |

**eTable 12.** Stone Clearance for Percutaneous Nephrolithotomy (PCNL) and Ureteroscopy (URS) Considering Sensitivity and Specificity of Ultrasonographic Images on Centralized Imaging Review, Overall and by Stone Size and Stone Location

|                                        | Weighted PCNL vs URS |                     |                       |
|----------------------------------------|-----------------------------|---------------------|-----------------------|
|                                        | PCNL                 | URS          | PCNL-URS       |
| Stone Clearance, %
(95% CI) | 63.9
(41.8-86.1)         | 70.5
(66.2-74.7) | -6.5
(-29.1-16.1)  |
| Stone size                      |                             |                     |                       |
| <7 mm                                  | 48.9
(0.0-100.0)         | 78.1
(72.2-83.9) | -29.2
(-85.2-26.8) |
| 7-10 mm                                | 42.9
(0.0-100.0)         | 64.1
(55.7-72.5) | -21.2
(-89.9-47.5) |
| 10-15 mm                               | 65.5
(29.6-100.0)        | 59.3
(45.5-73.1) | 6.2
(-32.2-44.6)   |
| >15 mm                                 | 93.1
(81-100.0)          | 51.4
(29.1-73.7) | 41.7
(16.3-67.1)   |
| Stone location                  |                             |                     |                       |
| Lower pole kidney                      | 44
(0.7-87.3)            | 60.7
(50.5-70.9) | -16.7
(-61.2-27.8) |
| Non-lower pole kidney                  | 68.1
(38.4-97.9)         | 55
(45.9-64.2)   | 13.1
(-18-44.2)    |
| Ureter                                 | 72.5
(28-100.0)          | 81.2
(75.8-86.6) | -8.7
(-53.5-36.1)  |

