| 7-10 mm                                                                                                                                                                                                                                          | 41.9
(0.0-90.6)          | 66.9
(61.2-72.7) | -25.0
(-73.7-23.8) |
| 10-15 mm                                                                                                                                                                                                                                         | 65.2
(30.4-100.0)        | 57.7
(44.2-71.3) | 7.5
(-27.6-42.5)   |
| >15 mm                                                                                                                                                                                                                                           | 81.1
(44.2-100.0)        | 60.3
(45.5-75.2) | 20.7
(-15.4-56.8)  |
| Stone location                                                                                                                                                                                                                            |                             |                     |                       |
| Lower pole kidney                                                                                                                                                                                                                                | 51.9
(13.3-90.5)         | 63.8
(54.2-73.3) | -11.9
(-52.9-29.1) |
| Non-lower pole kidney                                                                                                                                                                                                                            | 62.6
(24.5-100.0)        | 59.2
(52.7-65.7) | 3.4
(-35.5-42.2)   |
| Ureter                                                                                                                                                                                                                                           | 74.6
(39.9-100.0)        | 84.2
(80.6-87.9) | -9.7
(-43.9-24.6)  |

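### The SAP does not say that its imputation model contains the treatment interactions its HTE analysis estimates; without them, the difference for stones over 15 mm would be roughly halved

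*Combined protocol and SAP*

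**What the plan says.** The Missing data section of the SAP (eAppendix 1) gives the imputation inputs: "Variables used to impute missing data included all baseline covariates, treatment variable, and observed outcomes that were used in the analysis". It continues "Twenty imputed datasets were created and analyzed separately", with pooling by Rubin's rules, and sets the scope: "MI was used for the analyses of stone clearance, PROs at week 1, and HTE of both primary and secondary analyses". Stone size and stone location are confounders in eTable 1, so they can be taken to be among the inputs. The section gives no functional form, no interaction terms and no imputation within treatment arms.

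The SAP's HTE section says "HTE was analyzed by both stratified analyses and regression models with interaction terms". The modifiers are stone size (four groups) and stone location (three groups) for clearance, and age group and sex for the patient-reported outcomes (PROs). Protocol section 2.1 makes HTE by stone size and location part of the primary objective. Section 6.4 calls the HTE analyses descriptive and says they need not be powered. The SAP's Sensitivity analysis section adds: "We conducted a complete data analysis assuming the missingness was completely random".

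**The concern.** An imputation model should be at least as rich as the analysis model that uses its output. If missing clearances are drawn from a model with treatment and stone size but not their product, the imputed kidneys carry nearly the same treatment contrast at every stone size. Mixing them with the observed kidneys biases the subgroup contrasts even when outcomes are missing at random, and the bias grows with the share imputed. Here that share is more than half.

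The contrast for stones over 15 mm is the only clearance subgroup whose interval excludes zero in eTables 11 and 12. In eTable 13, after MI, the interval includes zero. A reader who regards the MI table as the better treatment of missing data could conclude that the large-stone difference comes from analysing complete cases, when the imputation model itself might have removed it. The same reasoning applies to PROs by age and sex, but the documents give nothing from which to size it.

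**Working it through.** **1. The plan's own figure.** eTable 13, over 15 mm: 81.1 - 60.3 = 20.8, printed as 20.7 (rounding). The interval midpoint is (-15.4 + 56.8)/2 = 20.7, and the implied standard error is (56.8 + 15.4)/(2 × 1.96) = 18.4.

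**2. Share without an analysed outcome (eTable 4, patients).**

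| | Enrolled | Analysed | Not analysed |
|---|---|---|---|
| PCNL, all | 93 | 46 | 47 (50.5%) |
| URS, all | 946 | 436 | 510 (53.9%) |
| Both, all | 1,039 | 482 | 557 (53.6%) |
| PCNL, over 15 mm | 36 | 17 | 19 (52.8%) |
| URS, over 15 mm | 43 | 17 | 26 (60.5%) |
| Both, over 15 mm | 79 | 34 | 45 (57.0%) |

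**3. MI against the other two tables, over 15 mm.** 20.7/41.7 = 0.50 (eTable 12) and 20.7/35.3 = 0.59 (eTable 11), a fall of 50% or 41%.

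**4. What the imputed cases must look like.** Imputed rate = (MI rate - observed share × observed rate)/missing share. With eTable 12 as the observed rates:
- PCNL: (81.1 - 0.472 × 93.1)/0.528 = about 70%
- URS: (60.3 - 0.395 × 51.4)/0.605 = about 66%

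The arms differ by about 4 points among imputed cases. With eTable 11 rates the figures are about 71% and 62%, a difference of about 9 points. On either basis the imputed cases carry little of the observed contrast.

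**5. What imputation without the interaction would give.** I fitted a logistic model with treatment and size category only to the observed counts (PCNL 7, 6, 11, 17; URS 194, 131, 48, 17, in increasing size) at the eTable 12 rates. For stones over 15 mm it predicts 73.7% (PCNL) and 70.8% (URS). Filling in the missing cases:
- PCNL: (17 × 93.1 + 19 × 73.7)/36 = 82.9
- URS: (17 × 51.4 + 26 × 70.8)/43 = 63.1
- Difference: 19.7 from unrounded values, where 41.7 went in

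With eTable 11 rates, the difference of 35.4 from the printed arm rates becomes 18.1. Entering size linearly gives 23.3 and 21.7. Fitting the model to the URS case mix in both arms gives 7 to 10.

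**6. Simulation.** With the same counts and eTable 12 rates as truth, 300 replicates and 20 imputations, imputation without the interaction averaged 19.8 points (SD over replicates 9.3). Imputation within each arm-by-size cell averaged 41.4 (SD 13.0).

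**7. The other subgroups (PCNL minus URS, points).** The overall difference in eTable 13 is -6.4.

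| Subgroup | eTable 12 | eTable 13 (MI) | Step 5 prediction | eTable 12 to 13, relative to -6.4 |
|---|---|---|---|---|
| Under 7 mm | -29.2 | -19.1 | -12.3 | towards |
| 7-10 mm | -21.2 | -25.0 | -12.9 | away |
| 10-15 mm | 6.2 | 7.5 | 4.9 | away |
| Over 15 mm | 41.7 | 20.7 | 19.7 | towards |
| Lower pole | -16.7 | -11.9 | not modelled | towards |
| Non-lower pole | 13.1 | 3.4 | not modelled | towards |
| Ureter | -8.7 | -9.7 | not modelled | away |

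The four subgroups that move towards the overall value move by 4.8 to 21.0 points. The three that move away do so by 1.0 to 3.8.

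**The case against.** A reader might infer that the interactions were left out and that this is what halved the large-stone effect. The documents do not support that, for four reasons.

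- The SAP lists variables, not a model. Imputation by arm, a tree-based method or unlisted product terms would all fit its sentence.
- The comparators are not like for like. eTable 12 is reweighted for the sensitivity and specificity found at central review, and eTable 11 uses a 0-16 week window. The plain complete-case subgroup estimate for 4-8 weeks is not in these documents.
- Shrinkage is not uniform. The calculation in step 5 matches the over-15-mm row but misses the two smallest size groups, and eTable 13 moves the other way for 7-10 mm. With 6 or 7 observed PCNL patients in each of those groups this does not refute the mechanism, but one matching row does not establish it.
- Chance and covariate differences remain possible. The gap of 21.0 points is 21.0/18.4 = 1.1 standard errors of the MI estimate, a rough gauge because the two estimates share data. The simulation takes eTable 12 as truth, so it shows only that the mechanism is large enough.

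Two observations weigh the other way. Both arms move inward from eTable 12 to eTable 13 (PCNL 93.1 to 81.1, URS 51.4 to 60.3), as a missing interaction predicts. Lost precision alone does not bring zero into the interval if 41.7 is the starting point: 41.7 ± 1.96 × 18.4 is 5.6 to 77.8. From 35.3 it is borderline, at -0.8 to 71.4.

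It can also be said that HTE is descriptive and that a complete-data analysis is planned. That excuses low power and an interval that crosses zero. It does not excuse a biased point estimate of an effect named in the primary objective and reported for later synthesis. For the PROs there is no sign of collapse: eTable 10 still shows anxiety contrasts of -11.1 at ages 8-11 and 12.49 at ages 19-21.

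**Conclusion.** The point stands as a gap in specification with a calculable consequence. Imputing from the listed variables with no interactions would reduce an over-15-mm difference of about 35 to 42 points to about 18 to 20 (up to about 23 if size enters linearly). The printed 20.7 is consistent with this but does not prove it. Until the model is stated, the MI subgroup results in eTable 13 cannot be told apart from an artefact of the imputation. The effect on the PRO subgroups is not quantified.

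The size rests on these assumptions: patients stand in for kidneys, the unit of analysis; enrolled patients outside the primary analytic cohort lack an in-window outcome; patients with no stone or with missing size are left out; inverse probability weighting and stone location are not modelled; and published rates are treated as observed rates.

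**What to change.** State the clearance imputation model in the SAP and make it compatible with the HTE analysis. Either include treatment × stone size and treatment × stone location, or impute by arm, or use substantive-model-compatible imputation. If the PCNL cells are too sparse, penalise the terms or enter size continuously; continuous size still does not match the four-category analysis exactly, and the SAP should say so. Do the same for treatment × age group and treatment × sex in the PRO imputation. Re-run eTable 13 and the PRO HTE, and show the plain 4-8 week complete-case subgroup estimates beside them. If the model already contained these terms, a sentence saying so and the complete-case estimates are enough.

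The cost is a few SAP sentences and a re-run. Subgroup intervals may become wider or less stable, with 6 to 17 observed PCNL patients per size group; in the simulation the spread of the over-15-mm estimate rose from 9.3 to 13.0 points. Using more than 20 imputations is optional: it lowers Monte Carlo error but does not address this bias.

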### Outcome model

Both the primary and secondary outcomes were compared using the IPW approach. The outcomes were compared using regression models with IPW and adjusted for unbalanced confounders after weighting. The analysis of PROs was conducted at 1-week, 3-weeks, 6-weeks, and 3-months after the index surgery adjusting for baseline scores.

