### Patient Experiences: Overall Treatment Effect.

For PROMIS measures, we will fit weighted linear mixed effects models to test the difference in T-scores after surgery across treatment options for each domain. Separate models will be built for outcomes at 1 week, 3 weeks, 6 weeks, and 3 months after surgery. We will also take advantage of the longitudinal nature of the PROs and fit WLMMs to compare the slopes of the PROs over time and the area under the curve.

Secondary patient experience outcomes, including number of emergency department visits, unplanned hospitalizations, and surgical retreatment will be compared across treatment options using weighted zero-inflated negative binomial regression models.

**SubAim 2a: HTE.** We will examine for HTE with interaction terms between procedure and patient age and procedure and sex to identify associations that differ for subgroups. We will also explore HTE by other patient participant characteristics including, but not limited to, ambulatory status.

**SubAim 2b: Effect modification by procedure-specific techniques.** We will stratify the data by treatments and, within each treatment; we will fit linear mixed effect models to test whether modifiable techniques are associated with patients' experiences for each procedure.

We will evaluate the change in outcomes across PKIDS after knowledge of best practices generated by the above analyses are integrated into clinical care. Our regression models will test differences in both the intercept (average value) and slope (change over time) for outcomes.

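### No imputation or other missing-data method is listed for the main PRO comparisons at 3 weeks, 6 weeks and 3 months, although earlier scores could inform them

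*Combined protocol and SAP*

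**What the plan says.** The Outcome model section of the SAP commits to four post-operative PRO comparisons: "The analysis of PROs was conducted at 1-week, 3-weeks, 6-weeks, and 3-months after the index surgery adjusting for baseline scores". The method there is weighted regression: "The outcomes were compared using regression models with IPW and adjusted for unbalanced confounders after weighting".

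The Missing data section opens generally, "We used multiple imputation (MI) to handle missing data", and describes the imputation model: "Variables used to impute missing data included all baseline covariates, treatment variable, and observed outcomes that were used in the analysis". It closes by stating where imputation was applied: "MI was used for the analyses of stone clearance, PROs at week 1, and HTE of both primary and secondary analyses". The later main PRO comparisons are not on that list.

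The Sensitivity analysis section adds two relevant items. One is "We conducted a complete data analysis assuming the missingness was completely random", which is not tied to any PRO visit. The other is a set of pattern-mixture scenarios "to assess the impact of potential missing not at random mechanisms on the study results for stone clearance". PROs have no counterpart to the second.

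Protocol section 6.3.2 (Patient Experiences) says "Separate models will be built for outcomes at 1 week, 3 weeks, 6 weeks, and 3 months after surgery". It then plans weighted linear mixed models across visits, to compare slopes and area under the curve. The SAP's Outcome model section does not carry these forward.

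**The concern.** Delayed impact is part of the secondary objective (protocol section 2.2 names the later assessments), and the multiplicity allowance in protocol section 6.4 counts all four post-operative times. Three of those four have no stated treatment of missing questionnaires.

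A per-visit regression without imputation uses whoever answered at that visit. A patient's week-1 score then contributes nothing when the 3-month score is missing, although it was collected and is probably a good predictor. Suppose patients who did well or badly at week 1 are more likely to stop answering. The later contrasts between procedures can then be biased, and the recovery curve changes its missing-data assumption between week 1 and week 3. Readers would compare week-1 and later estimates that rest on different conditions.

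**Working it through.** The plan gives no figure to reproduce here. The check has two parts.

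**1. The texts side by side**

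| Analysis | Imputation listed | Other missing-data method | Not-at-random sensitivity analysis |
|---|---|---|---|
| Stone clearance | Yes | Complete-data analysis | Yes |
| PROs, week 1 | Yes | Complete-data analysis (visit not specified) | None stated |
| PROs, 3 weeks, 6 weeks, 3 months (main comparisons) | Not listed | None assigned | None stated |
| Heterogeneity, primary and secondary | Yes, no time limit given | – | – |

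The PRO heterogeneity tables shown (eTables 9 and 10) are for week 1 only, so the last row does not show that later scores were imputed.

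**2. When would an observed-case, baseline-adjusted regression be biased?**

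I checked this by simulation. Only the cohort size and split come from the documents (eTable 4: 93 PCNL + 946 URS = 1039). Everything else is assumed, because the documents give no later-visit inputs. T = 1 for PCNL.

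- Baseline B: mean 50, SD 10.
- Week 1: Y1 = 20 + 0.6B − 5T + e, with SD of e = 8.
- Later visit: Y = 20 + 0.6B − 3.0T + 0.5e + noise, with noise SD 7. The true difference is −3.0.
- Log-odds of a missing later score: −0.4 plus the term in the table. This leaves 40–43% missing.
- Observed-case estimate: regression of Y on T and B among responders.
- Imputation estimate: missing Y predicted from T, B, Y1 and their interactions with T, then the same regression on everyone.
- 2000 replicates. Monte Carlo standard error of the observed-case mean is 0.024 to 0.030. Propensity weighting was left out for simplicity.

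| Missingness depends on | Term added | Observed cases | With imputation |
|---|---|---|---|
| Nothing | – | −3.04 | −3.03 |
| Baseline | 0.08(B − 50) | −2.98 | −2.98 |
| Baseline and arm | 0.08(B − 50) + 0.8T | −3.02 | −3.02 |
| Baseline, opposite by arm | 0.08(B − 50)(1 − 2T) + 0.5T | −3.03 | −3.06 |
| Week-1 score | 0.10(Y1 − 50) | −2.72 | −2.97 |
| Week-1 score, opposite by arm (deliberately extreme) | 0.10(Y1 − 50)(1 − 2T) | −0.32 | −2.98 |

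The first four rows show no detectable bias, although three of them are not missing completely at random. The last two are biased by −2.72 − (−3.0) = 0.28 and −0.32 − (−3.0) = 2.68 points. Protocol section 6.4 sizes Aim 2 for a 2-point difference. Imputation that uses the week-1 score removes the bias in both.

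A second route to bias was not simulated but follows from the design. Weights estimated for treatment choice balance confounders in the cohort in which they are estimated. They do not correct for who answers later. The SAP puts a confounder in the outcome model only if its standardized difference exceeds 0.25 after weighting. Other confounders sit in the propensity model alone, and their balance need not hold among responders.

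The documents make it plausible that response is related to arm. Protocol section 3.3.1 enrols patients who cannot or will not complete questionnaires, for clearance and record surveillance only. Developmental delay was recorded in 39.8% of PCNL and 11.9% of URS patients (eTable 4) and is not in eTable 1. Many of these patients would be missing at every visit, so this does not measure later attrition.

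**The case against.** The strongest reply is that the later analyses are not shown to be defective.

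A reader might infer that they are complete-case by rule and valid only if data are missing completely at random. The documents do not support either step. No sentence excludes later PROs from imputation or assigns them a complete-case analysis; the section's opening sentence is general and its closing list is simply silent about them. The sentence about completely random missingness describes a sensitivity analysis and is attached to no PRO visit. The condition is also too strict: with treatment and baseline score in a correct model, response may depend on both without bias, as the simulation rows on baseline and arm show. Response that merely differs by procedure is therefore not enough to cause bias.

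It is also fair to say that the protocol plans a longitudinal mixed model, which would use partial records and let earlier scores inform later ones.

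All of this stands, and it narrows the point without removing it. Because the list names week 1 specifically, the general opening cannot safely be read as covering the later visits. A per-visit regression without imputation is an observed-case analysis by default. The longitudinal model does not appear in the SAP section that defines the outcome analyses.

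**Conclusion.** The point holds as a cheap improvement. For three of the four post-operative PRO times, the main comparisons have no stated missing-data method and no sensitivity analysis for data missing not at random. Read naturally, they ignore post-operative scores already collected. They are valid if missingness depends only on treatment and covariates in a correctly specified outcome model. They can be biased if it depends on earlier post-operative PROs, or on outcome-related covariates used only for the propensity score.

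The size is unknown. Numbers observed at the later visits are not given; the protocol's 10% loss to follow-up for Aim 2 is only a planning assumption. The simulated range, no bias up to 2.68 points on a true difference of 3.0, shows the mechanism under assumed inputs and does not estimate the bias in this study.

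A reader might try to infer response from eTable 8, where the URS interval widths correspond to about 546 to 637 effective observations out of 946 enrolled. That does not support a later-visit attrition rate. The figures are for week 1, their widths may include imputation and weighting variance, and the denominator includes patients enrolled without questionnaires.

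The conclusion rests on reading the closing list as complete. If later PROs were in fact imputed or modelled longitudinally, the remedy is to say so.

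**What to change.** State the method for the later PRO comparisons in the SAP, and choose one of two:

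1. Extend the existing imputation (twenty datasets, Rubin's rules) to all four post-operative times. Use one imputation model that holds baseline and all post-operative PRO scores, treatment and the propensity covariates.
2. Make the protocol's weighted longitudinal mixed model the main analysis for the later times, and write it into the Outcome model section. Covariates thought to drive response should then be in that model, since the treatment weights do not handle dropout.

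In either case, keep the observed-case result as a sensitivity analysis and report the number observed by arm and visit. Neither option covers response that depends on the unseen later score itself. A shift in imputed scores by arm, similar to the pattern-mixture scenarios already used for stone clearance, would address that and is a small addition to option 1.

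The cost is SAP wording and some extra analysis work. No new data are needed.
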